#### AIM 1 procedures

Over the course of 8–12 weeks, we will evaluate OR-to-ICU handoffs as they currently take place in two surgical intensive care units (*inner setting)* in Philadelphia, Pennsylvania (*outer setting).* Although these ICUs are part of the same health system, they serve different surgical populations and are staffed by different types of providers (*individuals involved*; Table 1). Patients receiving care in the two study units live throughout the Delaware Valley and represent a diverse payor mix (Medicaid, Medicare, private payors) as well as indigent patients receiving uncompensated care (*outer setting*).

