**Table 1 Tab1:** **Study ICU characteristics**

	Study unit	
Characteristic	Study unit 1	Study unit 2
Surgical specialties represented	General, oncologic, orthopedic, otorhinolaryngologic, plastic, transplant, trauma, urologic, vascular	Cardiac, general, orthopedic, vascular
Beds	24	16
ICU model	Semi-closed*	
Clinicians	• Registered nurses	• Registered nurses
	• Attending physicians: ICU, surgery	• Attending physicians: ICU, surgery
	• Fellows: ICU, surgery	• Fellows: cardiac surgery
	• Residents: anesthesia, ICU, surgery	• Residents: anesthesia, ICU, surgery
	• Advanced practitioners: nurse practitioner	• Advanced practitioners: physician assistants, certified registered nurse anesthetists
Patient demographics	50% white, 49% black, 1% Asian, 9% other	

*“Semi-closed” indicates that each patient in the study units has two care provider teams – one surgical team and one intensive care unit team. Other models include “open” units where patients have just a surgical care provider team and “closed” units where patients have just an ICU provider team.

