#### AIM 1 measures

Aim 1 will address the question “How do OR-to-ICU handoffs occur in settings without a standardized process?” As we collect data to answer this question, we will also collect information to enable development of a standard handoff process. Given the hybrid nature of the study, we will measure concepts related to both effectiveness and implementation (Table 3). These are not true “outcomes” because they are collected at baseline, but they will enable us to detect changes occurring in the intervention phase:

**Table 3 Tab3:** **Study outcomes stratified by measure type (implementation vs. intervention) and data type (qualitative vs. quantitative)**

		Measure type	
		*Implementation*	*Intervention*
Data type	*Qualitative*	Acceptability (primary)	Handoff quality
		Appropriateness	
		Fidelity	
		Sustainability	
	*Quantitative*	Acceptability*	Information omissions, number (primary)
			Handoff accuracy
			Handoff duration
			Team members present, number
			Teamwork quality**
		Fidelity	Professionalism
			Diagnostic test utilization
			Medication orders
			Patient ICU length of stay
			Patient ICU mortality
			Patient hospital mortality

*Assessed with 5-point Likert scale.

**Assessed with 3-point scale.

Effectiveness outcome 1: Number of information omissions. Published studies demonstrate that important patient information is frequently omitted from OR-to-ICU handoff communication when these handoffs are not standardized [8, 12]. Using a data capture tool developed for this project (Additional file 1), we will determine how many data elements are absent from each handoff.

Effectiveness outcome 2: Handoff accuracy. To our knowledge, no studies to date have reported whether the information reported during OR-to-ICU handoff is actually true. As such, there are no validated measures of handoff accuracy. To attempt to determine whether OR-to-ICU handoffs are accurate, we will compare observed handoff content (for the five elements described above) to the patient’s medical record to calculate accuracy. Accuracy will be defined as the number of content areas correctly relayed during handoff divided by the number of content areas for which medical record data is available.

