Additional effectiveness outcomes: We will collect data about patient outcomes, including ICU and hospital mortality as well as ICU and hospital length of stay. We will collect data about resource utilization in the first 24 hours of ICU admission (e.g. diagnostic test utilization, medications). We will also measure process outcomes such as number of team members present, handoff duration, quality of teamwork (coded on a 3-point scale), and professionalism (coded on a 3-point scale).

Implementation outcome 1: Acceptability, defined as “the perception among implementation stakeholders that a given treatment, service, practice, or innovation is agreeable, palatable, or satisfactory” [25]. We know of no validated measures of acceptability in critical care or perioperative settings. Investigators in mental health have used semi-structured interviews and questionnaires to assess acceptability [25]. For our study, we will analyze survey data and interview/focus group transcripts to qualitatively characterize acceptability of the current handoff practice and that of a proposed standardized process. Drawing on CFIR, we will explore how the inner setting of each ICU and the individuals involved impact acceptability of a standardized handoff process as well as the other implementation constructs described below.

Additional implementation outcomes: Appropriateness, defined as the “perceived fit, relevance, or compatibility” of a standardized handoff process, and feasibility, defined as the extent to which a standardized handoff process can be carried out [25]. As with “acceptability”, we will qualitatively characterize these implementation outcomes.

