### Data analysis

Qualitative approach: We will use a grounded theory approach [22] to develop a codebook and to analyze qualitative data (transcripts from interviews and focus groups, field notes, video recordings). During the analytic process, we will consider how the CFIR constructs described above affect our effectiveness and implementation outcomes. We will also probe for differences between the two study sites that may impact the intervention’s implementation or effectiveness. NVivo 9.0 (QSR International, Doncaster, Victoria, Australia) will be used to manage qualitative data and to facilitate analysis. Qualitative data will be coded by two research personnel; disagreements will be adjudicated by a third person on the research team. We will use the inter-rater reliability function in NVivo to assure consistency in coding within and across coders. Data analysis will start during the data collection for Study Aim 1, allowing us to adjust data collection procedures to adequately explore emerging themes.

Quantitative approach: We will use descriptive statistics to characterize quantitative measures (Table 3). We will stratify our analysis by study unit, time of handoff (day versus night/weekend), elective versus emergency surgery, and surgical specialty. To test the hypothesis about changes in information omissions, we will conduct a Mann–Whitney U test comparing means before and after the intervention. In addition to comparing information omissions within ICUs before and after standardization of the handoff process, we will compare patient outcomes (ICU length of stay, ICU mortality, hospital mortality) in these two study units with contemporary outcomes from two similar non-study units within the same healthcare system. Using a difference-in-differences approach, this latter comparison will enable us to gauge the likelihood that changes in patient outcomes over time were attributable to our intervention or to secular trends. For the quantitative implementation outcomes acceptability and fidelity, we will the Mann Whitney U test to detect site differences in intervention acceptability and fidelity. Quantitative data analyses will be conducted using the Stata program (version 12, StataCorp LLC, College Station, Texas).

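### The only planned test of Likert acceptability compares the two sites without regard to clinician role, so a site difference may reflect role mix or role-specific response rather than the setting

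*Protocol article*

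**What the plan says.** The Data analysis section (quantitative approach) names one test for the quantitative implementation outcomes: a Mann-Whitney U test "to detect site differences in intervention acceptability and fidelity". The same paragraph gives the stratification factors: "We will stratify our analysis by study unit, time of handoff (day versus night/weekend), elective versus emergency surgery, and surgical specialty". Clinician role is not one of them. Descriptive statistics are planned for all quantitative measures in Table 3.

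Quantitative acceptability is "Assessed with 5-point Likert scale" (footnote to Table 3). Only the qualitative row of that table marks acceptability as primary, and the implementation hypothesis is to be judged qualitatively.

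On staffing, AIM 1 procedures says of the two units that "they serve different surgical populations and are staffed by different types of providers". Table 1 lists "Advanced practitioners: nurse practitioner" for unit 1 and "Advanced practitioners: physician assistants, certified registered nurse anesthetists" for unit 2. The fellows also differ (ICU and surgery against cardiac surgery). Registered nurses, attending physicians and residents are listed for both.

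AIM 1 measures, under acceptability, states that "we will explore how the inner setting of each ICU and the individuals involved impact acceptability". The survey goes to every clinician who takes part in these handoffs, and Table 2 lists them by role group.

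**The concern.** The test puts all of a site's respondents into one sample. If roles differ in how well they like the new process, and the sites differ in the roles that answer, the two samples can differ even when acceptability is the same at both sites within every role. The reverse can also happen: a real difference in setting can be masked by an opposite role mix. Unequal response rates by role would have the same effect, even among roles found in both units.

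The listed strata do not deal with this. Time of handoff and urgency are attributes of a handoff, not of a survey respondent, and specialty is not role.

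At stake is what the study concludes about the two ICUs. The article treats the setting and the individuals involved as separate influences on acceptability, and its one inferential test of the Likert item cannot tell them apart. The point concerns acceptability only. Fidelity is scored per observed handoff and does not depend on survey role mix.

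**Working it through.** **The plan's own figure.** The article gives no power or error figure for acceptability. Its only power figure, 95.7%, is for information omissions. It reproduces: 1.5 / (2 × √(2/48)) = 3.674; 3.674 − 1.960 = 1.714; Φ(1.714) = 95.7%. It has no bearing on this point.

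**Inputs from the article.** The role groups listed in Table 2 for the survey sum to 100 + 100 + 130 + 120 + 12 = 462 (the table states 460 and calls its numbers estimates; the text of AIM 1 procedures says more than 700). Nurse practitioners and physician assistants together are 12/462 = 2.6%. Residents and nurse anesthetists together are 120/462 = 26.0%. No role count is given by site.

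**Mechanism.** With two role groups and no site effect within role, the expected difference in mean score between sites is

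(difference in role share) × (difference in mean score between roles).

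With roles 0.90 Likert points apart, this is 0.03 × 0.90 = 0.03 points for a 3-point gap in share, 0.10 × 0.90 = 0.09 for a 10-point gap, and 0.30 × 0.90 = 0.27 for a 30-point gap.

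**Simulation (all settings are assumptions).** Reference role: 5, 10, 20, 40 and 25% in the five categories. Second role: a latent normal shift of 0.4 or 0.8 SD downward, which is 0.43 or 0.90 Likert points. The second role averages 25% of respondents over the sites, with its share differing by 0 to 30 percentage points. Respondents per site: 70, 115 or 231. No site effect within role; 1,500 runs per setting; two-sided 5% level. The Monte Carlo standard error at 5% is √(0.05 × 0.95/1500) = 0.6 points.

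Rejection rate of the unadjusted Mann-Whitney test (role effect 0.43 / 0.90 points):

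| Gap in role share | 70 per site | 115 per site | 231 per site |
|---|---|---|---|
| 0 points | 5.0% / 4.4% | 5.1% / 4.7% | 5.0% / 6.3% |
| 3 points | 4.3% / 5.2% | 4.5% / 5.8% | 5.6% / 4.6% |
| 10 points | 6.1% / 7.0% | 5.9% / 8.7% | 7.4% / 14.0% |
| 20 points | 7.9% / 13.1% | 8.3% / 18.7% | 13.4% / 32.7% |
| 30 points | 9.5% / 24.4% | 14.1% / 37.6% | 23.0% / 64.9% |

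The van Elteren test, stratified by role, was run on the same data. In stratum k, with rank sum W_k, E_k = n_1k(N_k + 1)/2, permutation variance V_k and weight w_k = 1/(N_k + 1), the statistic is Z = Σw_k(W_k − E_k)/√(Σw_k²V_k). It rejected in 3.9% to 5.7% of runs across all settings.

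**What the gaps mean in people.** With 231 respondents per site, a gap of 10, 20 or 30 points means about 23, 46 or 69 more members of a role at one site. If all 12 nurse practitioners and physician assistants belonged to one site, the gap would be 12/231 = 5.2 points. How many of the 120 residents and nurse anesthetists are nurse anesthetists, and where they work, is not stated.

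**The case against.** The strongest reply is that the unadjusted test is not wrong. Whether clinicians at one site accept the process more than those at the other is a fair overall question, and the rank test answers it. Staffing is part of what makes the sites differ. The rejection rates above are errors only for a different target, the site effect within role. This stands, and it is why the crude comparison can stay.

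The evidence for a different role mix is also thinner than Table 1 suggests. That table describes ICU staff, while the survey covers everyone who takes part in handoffs. The AIM #1 description has nurse anesthetists and physician assistants among those who may bring patients to the ICU in both hospitals, and nurses, attendings and residents are listed for both units. This also stands: a difference in respondent mix is plausible, but its size is not documented.

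A reader might infer three stronger things, none of which the article supports:
- *That a staffing difference will be reported as an effect of the setting.* Nothing says how a site difference would be interpreted.
- *That the primary implementation outcome is at risk.* Its primary form is qualitative, and there role is respected: focus groups are separate by role and advanced practitioners are interviewed individually. The aim of exploring setting and individuals is part of that largely qualitative work.
- *That a false rejection rate of a half or more is to be expected.* Rates of that order need about a 30-point gap in role share, a large role effect and near-full response.

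Finally, adjustment for a supplementary measure could sit in a fuller plan not shown. But the article does name its test and its strata, and role is in neither.

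**Conclusion.** The point holds in a limited form. The one inferential test fixed for Likert acceptability cannot separate the setting from the role mix of respondents, which the article itself treats as distinct influences. A role-stratified comparison would answer that question better.

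The size cannot be determined, because role counts by site, response by role and differences between roles are not given. Under the assumed settings, rejection with no within-role site effect stays near the nominal level for a 0-3 point gap in role share, is 6-14% at 10 points, 8-33% at 20 and 10-65% at 30. The upper ends belong to 231 respondents per site and roles 0.90 Likert points apart.

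The measure is supplementary. The qualitative acceptability outcome and the effectiveness hypothesis on information omissions are untouched.

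**What to change.** In the quantitative part of Data analysis:
- Keep the Mann-Whitney comparison and label it as a description of the overall site difference, role mix included.
- Add a site comparison stratified by individual clinician role: a van Elteren test, or ordinal logistic regression with site and role.
- Define nurse practitioner, physician assistant, nurse anesthetist and resident as separate roles. Table 2 merges the first two into one group and the last two into another. If those roles are distributed as Table 1 lists them, strata built on the merged groups would keep the confounding inside the stratum.
- Report acceptability by site within role. Describe roles whose respondents come from one site only, and leave them out of the stratified test.

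The cost is a sentence or two of analysis wording, provided that the survey records role at this level. The downside is that single-site roles tell the stratified test nothing and the smallest strata add little.

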## Background

Handoffs are transfers of patient care and accountability that are a well-recognized risk factor for adverse events in healthcare such as medication errors [1] and delays in diagnosis or treatment [2]. Handoffs are ubiquitous in medicine due to the specialization of care across providers, disciplines and care settings [3]. Despite mounting evidence that handoff standardization is beneficial [4–13], variability in handoff processes persists in all the areas associated with surgical and anesthetic practice [14]. Of particular concern is the handoff occurring for patients admitted from the operating room (OR) to the intensive care unit (ICU). This transfer is high risk because it involves physical movement of patients and multiple handoffs among providers of different disciplines (anesthetist to critical care clinician, surgeon to critical care clinician, operating room nurse to critical care nurse, *et cetera*) [15]. Also, the patients whose care is transferred are often incapacitated and thus unable to participate, making them vulnerable to error and preventable harm.

Published reports demonstrate improved information exchange [5, 7–12] and improved patient outcomes [4, 9] when *cardiac* OR-to-ICU handoffs are standardized, especially in pediatric cardiac populations [7–12]. Though the findings from this work are intriguing, it is unclear whether the approaches adopted in postoperative pediatric cardiac care apply to *all* patients requiring postoperative critical care. Heterogeneous patient groups have differing levels of acuity and different nursing needs. Additionally, a larger number of potential procedures and providers may complicate the adoption of and adherence to a standard process. The proposed project aims to adapt previously published approaches to handoff standardization and to implement a handoff process that will be applicable to the care of patients undergoing cardiac, general surgical, orthopedic, transplant, trauma, and vascular surgical procedures.

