Implementation Strategy 1 - Planning: The needs assessment (Aim 1) described earlier is the first part of the planning process. Once we analyze data from the needs assessment, we will share our findings with physician and nurse leaders in each ICU (“champions”). We will work with these champions to create a new handoff process that incorporates elements from published studies (Figure 2) as well as important themes emerging from the needs assessment (Aim 2). We will also work with ICU champions to troubleshoot problems with implementation. Anticipated problems with implementation include the following: tool availability and ease of use, patient physiologic instability distracting from the process, clinician familiarity with the tool and the process, and clinician reluctance to adopt a new process. The research team will take detailed field notes during planning sessions with local champions.

Implementation Strategy 2 - Education: We will hold meetings of nursing and physician staff to share the results of the needs assessment and process development and to share the plan for implementation. Clinicians’ concerns will be addressed during these meetings and recorded with field notes taken by the research team. The handoff process will be adapted to account for these concerns. The research team will develop a glossary of terms related to the handoff process that will serve as an enduring reference, and the research team will be available in- person, by telephone, and via electronic mail during the study period for consultation as needed. We have created a study website (http://www.pennhatricc.com) that will serve as an additional educational resource for clinical staff and anyone with questions related to the study.

Implementation Strategy 3 - Restructuring: We will facilitate relay of clinical data from the OR team to the ICU team by making the handoff tool part of the patient’s bedside (nursing) chart. In this way, written information will be available to supplement and reinforce the verbal information transmitted during the handoff process. We will work with our local champions to facilitate this restructuring.

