**Handoff observation stratification scheme.**

Quantitative data: As the study is a Type 1 hybrid effectiveness-implementation trial, [16] power calculations are based on our effectiveness hypothesis. Previously published work suggests that, on average, 36-40% of handoff information is omitted in the absence of a standardized handoff process [7, 8]. After institution of a standardized process, information omissions drop by 50-66% [7, 8]. Our handoff observation tool has 13 content items; if our observations are consistent with published work, we will observe 4–5 omissions per handoff episode. We are assuming a standard deviation of 2 information omissions given the heterogeneity of this process, although others have reported a smaller standard deviation [7]. If these assumptions hold true, we will have 95.7% power to detect a drop in information omissions from 4.5 to 3 (a 33% drop), based on a sample size of 96 (48 pre-intervention, 48 post-intervention), and a two-tailed alpha of 0.05. The power calculation suggests that our target sample size for qualitative data will also be sufficient to detect pre- and post- intervention differences in our primary quantitative outcome (Table 3).

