Mixed methods approach: We will convene at least three members of the research team to characterize observed handoffs in Aims 1 and 3 as “satisfactory” or “unsatisfactory” on the basis of field notes and data from our handoff checklists. Once handoffs have been categorized in this way, we will re-analyze our quantitative outcomes (mortality, length of stay, resource utilization, etc.), stratifying them by the quality of handoff. We will perform this analysis with Aim 1 data alone to study the relationship between “good” handoffs and patient outcomes in the absence of a standard handoff process, and will also perform this analysis again once we have Aim 3 data.

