**Table 4 Tab4:** **Implementation strategy categories and specific approaches***

Planning	Education	Restructuring	Quality mgmt.
• Needs assessment (SA1)	• Implementation glossary	• Facilitate relay of clinical data to providers	• Audit and provide feedback
• Prepare champions	• Educational meetings		• Purposely re-examine implementation
• Formal blueprint			
• Consensus discussions	• Ongoing consultation		

*Categories from Powell *et al*. [27].

There are several strengths to this project as well. First, the hybrid effectiveness- implementation structure will enable us to contribute to the body of scientific work about improving postoperative communication while offering implementation findings that may be of use to other investigators. Second, the mixed methods approach will allow us to develop a comprehensive understanding of the handoff process from the perspectives of all the clinicians involved, improving our ability to develop and implement a feasible and acceptable intervention. Third, collecting data on both process outcomes (e.g. information omissions, teamwork quality) and patient outcomes (e.g. mortality, length of stay), will allow us to test the relationship between handoff quality and patient outcomes, a relationship that is assumed but not explicitly tested in many handoff studies. Lastly, the focus on a mixed surgical population extends the scope of work done by other investigators, increasing the potential impact of this work.

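### The comparison of patient outcomes by satisfactory versus unsatisfactory handoff is open to confounding by patient acuity and cannot support the claim to test that relationship

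*Protocol article*

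**What the plan says.** Data analysis, mixed methods approach: the handoffs observed in Aims 1 and 3 are sorted into two groups "on the basis of field notes and data from our handoff checklists". Then "we will re-analyze our quantitative outcomes (mortality, length of stay, resource utilization, etc.), stratifying them by the quality of handoff". This is done first in Aim 1 data alone, "to study the relationship between “good” handoffs and patient outcomes in the absence of a standard handoff process", and again once Aim 3 data are available. No covariate is named.

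Data analysis, quantitative approach: "We will stratify our analysis by study unit, time of handoff (day versus night/weekend), elective versus emergency surgery, and surgical specialty". The mixed methods paragraph does not say whether these strata also apply to the comparison by handoff label.

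Three places bear on acuity:
- Background: "Heterogeneous patient groups have differing levels of acuity and different nursing needs".
- AIM 2 procedures, Implementation Strategy 1: the anticipated problems include "patient physiologic instability distracting from the process".
- Sample size and power considerations: handoffs may differ between day and night, and between elective and emergency surgery.

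The strengths paragraph of the Discussion says that collecting process and patient outcomes together "will allow us to test the relationship between handoff quality and patient outcomes". The limitations paragraph covers the uncontrolled pre-post design but does not mention confounding in this comparison.

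**The concern.** The label is not assigned by design. It is a judgement on a handoff that took place around a particular patient. If an unstable or emergency patient makes an orderly handoff harder and is also more likely to die, stay longer or need more tests and drugs, the two groups will differ in outcome whether or not the handoff matters.

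The article states both a method (splitting outcomes by the label) and an inference (a test of the relationship). A covariate list in a fuller analysis plan could improve the method, but it would not correct the published inference. At stake is the one analysis the article describes for linking handoff quality to patient outcomes, a link the authors say is often assumed and rarely tested. A confounded answer could be cited as evidence that better handoffs improve outcomes, or that they do not.

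**Working it through.** **The plan's own figure.** No figure is given for this analysis. The only stated power, 95.7%, is for omissions, "based on a sample size of 96 (48 pre-intervention, 48 post-intervention), and a two-tailed alpha of 0.05". Check: 1.5 / (2 × √(2/48)) = 1.5 / 0.408 = 3.674; 3.674 − 1.960 = 1.714; Φ(1.714) = 0.957. It reproduces, but it does not bear on the comparison by label.

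**Confounding with a true handoff effect of zero.** The documents give none of the inputs, so all are assumptions:
- proportion of patients unstable, u: 10-30%
- unsatisfactory label: 30% of stable patients (a), 50-70% of unstable patients (b)
- mortality: 4-5% if stable (m0), 12-20% if unstable (m1)
- ICU stay doubled if unstable

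Formulas:
- P(unstable | unsatisfactory) = u·b / [u·b + (1−u)·a]
- P(unstable | satisfactory) = u(1−b) / [u(1−b) + (1−u)(1−a)]
- mortality in a group = m0 + (m1 − m0) × P(unstable | group)
- geometric stay ratio = 2 raised to the difference between the two proportions

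Worked case, u = 0.20, a = 0.30, b = 0.70, m0 = 5%, m1 = 20%:
- P(unstable | unsatisfactory) = 0.14 / 0.38 = 0.368
- P(unstable | satisfactory) = 0.06 / 0.62 = 0.097
- mortality 5% + 15% × 0.368 = 10.5% against 5% + 15% × 0.097 = 6.5%; ratio 1.63
- stay ratio 2^0.271 = 1.21

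| Scenario | Mortality ratio, unsatisfactory v satisfactory | Stay ratio |
|---|---|---|
| u 10%, label 30% v 50%, mortality 4% v 12% | 1.14 | 1.06 |
| u 20%, label 30% v 70%, mortality 5% v 20% | 1.63 | 1.21 |
| u 30%, label 30% v 70%, mortality 5% v 20% | 1.71 | 1.27 |
| Label unaffected by instability (30% v 30%) | 1.00 | 1.00 |
| Unstable patients rated better (stable 50%, unstable 30% unsatisfactory) | 0.76-0.89 | 0.89-0.95 |

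Within strata of instability every ratio is 1.00, because instability is the only confounder built in and is taken as measured.

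**Would it reach significance?** In the scenarios where instability worsens the rating, the chance of a significant mortality difference in the spurious direction (normal approximation, two-sided 0.05) is 3.5-9.5% with 48 handoffs and 4-14% with 96. For stay, simulated with 4,000 runs per scenario and a log SD of 0.8, the chance of a significant result is 5-15% and 6-28%. The median stay is longer in the unsatisfactory group in 57-79% of runs at 48 and 59-87% at 96.

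**Precision.** At an assumed 5-10% mortality, Aim 1 with 48-60 patients yields 48 × 0.05 = 2.4 to 60 × 0.10 = 6 deaths. For a 24 v 24 split, the 95% half-width is 1.96 × √(2p(1−p)/24), which is 12 points at 5% and 17 points at 10%.

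**Could the existing strata do the work?** Unit × time × urgency gives 8 cells. 48 / 8 = 6 handoffs per cell on average, or 3 per label group if the labels split evenly, before specialty (Table 1 lists nine for Study unit 1).

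**The case against.** The strongest reply is that the quantitative approach already stratifies by unit, time, urgency and specialty, and that the mixed methods re-analysis can be read as adding the label to those strata. If so, confounding by urgency is partly handled. An example built on urgency alone (mortality 12% emergency, 3% elective; emergencies 70% of unsatisfactory and 30% of satisfactory handoffs) gives 9.3% v 5.7%, but its ratio within strata is 1.00. This stands in part: calling the analysis wholly unadjusted would read too much into silence. But the carry-over is not stated, the cells are too thin to use jointly, and none of the strata measures severity or stability.

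A reader might also infer that the analysis is bound to show good handoffs linked to better outcomes. The documents do not support that. The instability remark is one anticipated difficulty in introducing the new process, not a finding about baseline handoffs or ratings. Emergency handoffs are said only to be possibly different, not worse. The bias could be nil or reversed, and at 48 to 96 handoffs a false significant result is unlikely in every scenario tried.

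Three further inferences are possibilities only:
- **Raters knowing outcomes.** The label's stated inputs are field notes and checklists. The research team does abstract postoperative records, but the article does not say the abstractors are the raters.
- **Confounding by phase.** Aim 1 is analysed alone first, and pooling with Aim 3 is not stated.
- **Circularity.** Omissions are not named among the outcomes compared by label; they could enter only through the open-ended end of that list.

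Finally, the analysis is secondary. That limits the weight of the point but does not remove it, because the Discussion presents the resulting inference as a strength.

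**Conclusion.** The point holds in a limited form. As described, the comparison by label can be confounded by acuity, which the article's own text suggests may relate to how handoffs go, and it cannot carry the claim to test the relationship. With no true effect, the assumed inputs give spurious mortality ratios of about 1.1 to 1.7 and stay ratios of about 1.06 to 1.27 if instability worsens the rating. The ratios are 1.00 if it does not, and below 1 if unstable patients are rated better. Which case applies cannot be settled from the documents. Any mortality comparison in Aim 1 is in any event very imprecise, with about 2 to 6 deaths expected under the assumed mortality. The primary outcome and its power calculation are not affected.

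**What to change.** 1. Assign the satisfactory/unsatisfactory label before anyone on the rating panel views outcome data.
2. Compare length of stay and resource use with adjustment for a small fixed set: elective or emergency surgery, study unit, and one pre-handoff severity proxy from the pre- and intraoperative record. Add phase if Aims 1 and 3 are pooled. List deaths by group as counts, without a test.
3. Do not compare checklist-derived outcomes, such as omissions, by a label built partly from the checklist.
4. In the Discussion, replace the claim of a test with an exploration of the association, and add confounding by acuity to the limitations.

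The cost is modest: the order of existing tasks, a few covariates and some wording. The focused chart review names no severity score, so a proxy has to be chosen from what it abstracts, for example medication infusions or intraoperative fluid balance. A proxy leaves residual confounding. Adjustment in 48 to 96 patients widens the intervals, so the covariate set must stay short. The published claim becomes softer.
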